## Abstract

**Background:**

Wellness my Way is a chronic disease prevention model of care being piloted across South West Queensland, Australia, a region of high chronic disease burden. Wellness my Way is an initiative of the Queensland Government through Health and Wellbeing Queensland, delivered in partnership with Queensland Health’s Health Contact Centre and South West Hospital and Health Service, supported by multisectoral collaborations.

**Objective:**

This protocol aims to describe the development of Wellness my Way and the protocol for evaluating the program’s pilot implementation.

**Methods:**

The context for the Wellness my Way pilot and the multisectoral approach and co-design activities that informed program development and implementation are described. The RE-AIM (Reach, Effectiveness, Adoption, Implementation, and Maintenance) framework has guided the evaluation. The primary outcome is the uptake (reach) of Wellness my Way. Secondary outcomes include consumer satisfaction and stakeholder experiences. Data were derived from quantitative and qualitative measures collected from consumers and stakeholders.

**Results:**

Ethics approval has been granted. The Wellness my Way pilot program within South West Queensland, Australia, concluded in January 2026, with findings anticipated to be shared in late 2026.

**Conclusions:**

The findings will offer new insights on the impact of a collaboratively delivered program in a community with high unmet needs.

## Introduction

Noncommunicable diseases (NCDs) are complex health conditions that can lead to lower quality of life and shorter life expectancy [1]. Many NCDs are linked to modifiable risk factors such as consumption of a poor diet, physical inactivity, overweight and obesity, smoking, and harmful drug and alcohol use [1,2]. In Australia, 1 in 2 people are living with at least 1 NCD [3]. In 2023‐2024, NCDs accounted for two-thirds of the total burden of disease, 52% of hospitalizations, and 89% of deaths, and contributed to AUD $82 billion (US $58 billion) in health care expenditure [4-6]. For regional and rural Australians, higher rates of NCDs are experienced with 67% of these residents living with at least 1 condition compared to 58% of metropolitan residents [7]. Australians living in these areas disproportionately report higher rates of behaviors associated with poorer health outcomes, compared to those living in major cities, influenced by barriers in health infrastructure and the provision of health care services and prevention [7,8].

The 2022 Australian National Health Survey reported 52% of residents in the Australian state of Queensland were living with at least 1 NCD [8]. Most recent estimations from 2011 to 2012 found that health expenditure in Queensland associated with NCDs was estimated at AUD $9.6 billion (US $6.8 billion) [9]. Fragmented health care systems, time and financial constraints, and workforce shortages have created barriers to prevention efforts [10]. Limited community knowledge of prevention, lack of awareness of NCDs, and low engagement in behavior change have also been reported as barriers [11].

A range of free and low-cost prevention programs are available to Queenslanders; however, gaps in awareness, health literacy, geographical barriers, and complex service pathways have reportedly contributed to poor uptake [12]. To address this, a prevention model of care, Wellness my Way [13], was designed, led, and funded by Health and Wellbeing Queensland (HWQld), in partnership with Queensland Health’s Health Contact Centre (HCC), Queensland Health’s South West Hospital and Health Service’s (SWHHS) Healthy Communities Team, and the Health and Wellbeing Centre for Research Innovation (HWCRI) at The University of Queensland (UQ). Wellness my Way is a free, personalized approach to prevention piloted in South West Queensland [13]. The program seeks to increase the uptake of prevention programs through a community-led, streamlined approach, including an online health and well-being assessment and telephone-delivered coaching to co-design a personal well-being action plan. This program leverages a pre-existing prehabilitation model of care delivered by HCC, Way to Wellness.

Health coaching is an evidence-informed approach to health promotion with digital health improving reach and scalability [14,15]. The program uses a place-based approach to build preventive health capacity in local workforces, integrate prevention into existing systems, and connect consumers to existing prevention programs and services [16].

The objective of this study is to describe the development of, and the evaluation protocol for, Wellness my Way. We outline the program’s context and setting, and describe the multisectoral approach and co-design activities which led to the program’s development, recruitment, and delivery. The detailed evaluation protocol is also described.

## Methods

The Template for Intervention Description and Replication–Population Health and Policy (TIDieR-PHP) interventions [17] and Expert Recommendations for Implementing Change (ERIC) strategies [18] were used to guide the reporting of this protocol. The Wellness my Way pilot was delivered from July 29, 2024, to June 30, 2025, with follow-up data collection until January 29, 2026.

### Context and Setting

The Wellness my Way pilot was conducted in the South West region of Queensland, in Queensland, Australia. In 2022, South West Queensland had a population of 24,173 (50% female), and 56% were aged between 20‐64 years [19]. In 2025, 16% of South West Queensland identified as First Nations [20]. Recent data estimate that South West Queensland adults experience high rates of modifiable risk factors, with just over two-thirds living with overweight or obesity, and almost 50% do not engage in sufficient levels of physical activity [21]. Over 90% reported inadequate consumption of vegetables, 27% reported risky alcohol use, and 13% reported smoking daily [21].

### Program Development

In 2022, HWQld, Queensland Government’s statutory agency for chronic disease prevention, set out to improve awareness, navigation, and uptake of prevention programs. Stakeholder consultation explored both clinician- and consumer-facing solutions, identifying an opportunity to work collaboratively with the health system to test a free, consumer-facing digital pathway to a prevention program in Queensland leveraging the HCC Way to Wellness prehabilitation model of care. Key elements of Way to Wellness include SMS text message invitation, online health assessment to identify modifiable risk factors, provision of brief advice in line with Australian clinical guidelines, telephone coaching using motivational interviewing to develop a wellness action plan delivered by a preventive health counselor, promotion of the role of general practitioners in supporting the consumer to make health changes (including sharing of the wellness action plan), and offer of connecting consumers with prevention programs while awaiting orthopedic surgery [22]. HWQld and HCC collaboratively adapted the Way to Wellness model to be accessible for more Queenslanders to support early identification and reduce modifiable risk factors for those at risk for, in the early stages of, or living with NCDs [23].

South West Queensland, a region with high burden of NCDs, was considered an appropriate setting for the Wellness my Way pilot, with implementation supported by an existing memorandum of understanding and strategic alignment between HWQld and SWHHS. The SWHHS’ Healthy Communities Team were engaged as the local implementation partner, bringing knowledge of the regional context and guiding engagement with the community.

Subsequently, HWQld led the development of a place-based implementation plan focused on collaboration, community activation, building workforce capability, and shared responsibility. This was achieved through in-person and online consultations with SWHHS’ Community Advisory Networks and local stakeholders to gather feedback on the model of care, identify local referral pathways, and inform implementation opportunities, including the design of a localized marketing campaign.

In 2023, leveraging an established partnership with UQ through a jointly funded research center by HWQld and UQ, HWQld partnered with HWCRI for expert consultation on health behavior change, research, and leading the evaluation of the Wellness my Way pilot.

The development phase culminated in a multisectoral partnership, led and funded by HWQld, that included Queensland Health’s SWHHS Healthy Communities Team for local implementation, Queensland Health’s HCC for delivery of the model of care, and HWCRI at UQ for research and evaluation.

### Model of Care

Wellness my Way involves 3 primary components. First, Wellness my Way invites consumers to complete a health and well-being assessment online or via telephone to assess current health status [13]. Using validated tools [24-26], questions explore the consumer’s self-reported health behaviors, including nutrition, physical activity level, mental health status, smoking, and drug and alcohol use; biometrics such as height, weight, and blood glucose level history; and demographics. A summary of the health and well-being assessment is emailed to the consumer. Next, within 1 week of the assessment, a preventative health counselor from the HCC contacts the consumer. Applying motivational interviewing skills [27], the preventative health counselor works with the consumer to co-design individual goals and create a well-being action plan, and provide referrals to free or low-cost, locally accessible prevention programs and services. The well-being action plan is shared with the consumer and, upon consent, shared with their nominated primary care professional. The consumer then continues their health journey with the support of the identified prevention programs or pathways.

Prevention programs available to consumers include a range of free and low-cost programs delivered locally (eg, SWHHS Community Dietitian, SWHHS Exercise Physiology, Parkrun), or at a state or national level (eg, Quitline, My health for life), all focused on supporting health behavior change. Programs may be delivered online, via phone, or in person. Consumers can be directly referred into programs with established referral pathways (upon consent) or provided program information for self-enrollment.

### Consumer Eligibility

Wellness my Way is available to individuals 18 years and older, and is most suited for those at risk of developing or living with NCDs. Pregnant people or those younger than 18 years are not eligible to participate. While not exclusively available to people living in South West Queensland, pilot recruitment is intentionally targeted toward residents living in this region.

### Recruitment

Consumers were recruited using a range of strategies, including community activation, local marketing campaigns, and waitlists. Recruitment via specialist outpatient waitlists was undertaken by HCC, consistent with the existing prehabilitation model of care. Eligible patients on South West Queensland category 2 (semiurgent specialist consultation) and 3 (nonurgent specialist consultation) waitlists received an SMS text message invitation linking to the online health and well-being assessment.

### Implementation Strategies

The Wellness my Way pilot program used a range of implementation strategies described in detail below and summarized in Table 1, where the primary implementation strategies are mapped according to Powell et al’s [18] ERIC strategies.

**Table 1. T1:** Wellness my Way implementation activities mapped to Expert Recommendations for Implementing Change (ERIC) strategies.

ERIC strategies	Connectors	Learning workshops	Marketing	Resources	Partnerships^a^
Access new funding					✓
Assess for readiness and identify barriers and facilitators					✓
Audit and provide feedback		✓			✓
Build a coalition	✓	✓			✓
Capture and share local knowledge	✓	✓			✓
Conduct cyclical small tests of change	✓	✓			
Conduct educational meetings	✓	✓			✓
Conduct educational outreach visits	✓	✓			✓
Conduct local consensus discussions	✓	✓			
Conduct local needs assessment					✓
Conduct ongoing training		✓			
Create a learning collaborative	✓	✓			✓
Develop a formal implementation blueprint				✓	✓
Develop academic partnerships		✓			✓
Develop an implementation glossary				✓	
Develop and implement tools for quality monitoring					✓
Develop educational materials			✓	✓	✓
Develop resource sharing agreements					✓
Distribute educational materials	✓	✓			✓
Facilitate relay of clinical data to providers	✓				✓
Facilitation	✓	✓			✓
Fund and contract for the clinical innovation					✓
Identify and prepare champions	✓	✓	✓		
Identify early adopters	✓	✓			
Increase demand	✓		✓		
Inform local opinion leaders	✓	✓			✓
Intervene with patients/consumers to enhance uptake and adherence	✓	✓			
Involve executive boards					✓
Involve patients/consumers and family members	✓		✓		
Make training dynamic	✓	✓			
Mandate change					✓
Model and stimulate change					✓
Obtain and use patients/consumers and family feedback	✓				✓
Obtain formal commitments	✓				✓
Organize clinician implementation team meetings	✓	✓			✓
Promote adaptability	✓	✓			✓
Promote network weaving	✓	✓			✓
Provide local technical assistance	✓	✓		✓	✓
Provide ongoing consultation		✓			✓
Purposely reexamine the implementation		✓			✓
Recruit, designate, and train for leadership					✓
Remind clinicians	✓	✓	✓	✓	✓
Revise professional roles	✓				
Shadow other experts	✓	✓			✓
Stage implementation scale-up	✓	✓	✓	✓	✓
Start a dissemination organization					✓
Tailor strategies	✓	✓	✓	✓	✓
Use advisory boards and workgroups	✓	✓			✓
Use an implementation advisor					✓
Use data experts					✓
Use data warehousing techniques					✓
Use mass media	✓		✓		
Use train-the-trainer strategies	✓				

a Partnerships describe the collective work between Health and Wellbeing Queensland, Queensland Health’s South West Hospital and Health Service, Queensland Health’s Health Contact Centre, and Health and Wellbeing Centre for Research Innovation. Only relevant strategies are included in this table.

### Training of Preventive Health Counselors

Prior to the pilot launch, HWQld and SWHHS delivered and recorded an online training session to upskill HCC preventive health counselors. This included aims and objectives of Wellness my Way, and regional needs of those living in South West Queensland, including geographic, social, and contextual factors such as limited transport, geographical distances, and harsh climates. Ongoing training was facilitated by local program leads (eg, community dietitian, mental health professionals) to inform counselors of regional services.

### Connectors

HWQld and SWHHS identified, supported, and upskilled local “Connectors”—local voices who advocate for, raise awareness of, and encourage participation in Wellness my Way. This approach was designed to make prevention a shared responsibility across the community, creating multiple entry points into Wellness my Way and prevention programs [28]. Connectors could be situated in settings such as local government, hospitals, pharmacies, allied health, general practices, Aboriginal and Torres Strait Islander Controlled Health Organizations, workplaces, nongovernment organizations, local businesses, community centers, and support groups.

HWQld invited South West community and social service organizations and health services to submit an Expression of Interest to assist implementation and embed Wellness my Way within their current service delivery. Each participating organization established a team of Connectors responsible for actioning Wellness my Way within their own organization. HWQld and SWHHS supported interested organizations and their identified Connectors via informal online check-ins to support continuous quality improvement, mitigate any issues, and drive motivation.

### Marketing Campaign

HWQld led the design and delivery of a locally tailored marketing campaign across South West Queensland during the pilot. Informed through community consultation, locally representative messaging that featured local faces and places were delivered through print and paid digital media channels to reach people in everyday settings and encourage completion of the health and well-being assessment. Physical materials (eg, recipe cards, flyers, posters, stickers, and coasters) included a QR code. Billboards were displayed on main roads throughout the region. Materials were disseminated by Connectors and the local implementation team at community events, health services, community meeting places, local businesses, and online.

### Learning Workshops

Led by HWQld, Connectors were invited to attend 4 learning workshops during the pilot to reflect on data, share learnings, receive support from HWQld and SWHHS, and identify and test avenues to better integrate the program within their organization (Figure 1). Learning workshops were informed by an adapted collaborative methodology [29], which supports shared, community-led action and continuous quality improvements to embed the program into local implementation systems.

**Figure 1. F1:**
[figure not shown]
Wellness my Way collaborative methodology implementation strategy (Queensland Government, Health and Wellbeing Queensland, 2025).

### Resources to Support Local Implementation

Informed by a desktop review, HWQld designed specific resources to support Connectors to effectively plan and implement change throughout the pilot. The Implementation Toolkit was developed to support organizations participating in the learning workshops with application of continuous quality improvement principles and testing of implementation approaches within their organizational and community contexts. It includes a Team Action Plan, an adapted version of The Model for Improvement [30], and supports identification of context-specific implementation approaches for iterative testing during the pilot.

The Connector’s guide is an abridged version of the Implementation Toolkit designed for a broader range of stakeholders acting as Connectors across the region, providing an overview of the prevention model of care and guidance to promote Wellness my Way within their communities. Both resources contain a list of prevention pathways on offer and guidance on how to have proactive and supportive conversations with prospective consumers [23]. HWQld has also designed a dedicated website [13], which features further resources to assist pilot implementation.

### Evaluation Protocol for Wellness My Way Pilot Prevention Model of Care

Wellness my Way is a health promotion program delivered by the Queensland Government. A comprehensive evaluation protocol was collaboratively designed by HWQld and HWCRI to examine program uptake, effectiveness, implementation experiences, and sustainability. All data that will be used in the evaluation were collected as part of routine service delivery by Queensland Health and HWQld, with data used for research purposes by UQ.

### Study Design

The evaluation will use a mixed methods approach, guided by the RE-AIM (Reach, Effectiveness, Adoption, Implementation, and Maintenance) framework [31]. Effectiveness will be assessed using a pragmatic single-arm, pre-post study design.

### Objectives

The evaluation of the Wellness my Way pilot aims to address 9 research objectives (Table 2). The primary objective is uptake (reach) of Wellness my Way (research objective 1) with secondary objectives evaluating program effectiveness, adoption, and implementation experiences.

**Table 2. T2:** Wellness my Way pilot evaluation research objectives.

Research objective	RE-AIM^a^ principle
1. What is the reach of Wellness my Way?	Reach
2. What was the uptake of prevention programs as a result of Wellness my Way?	Effectiveness
3. What is the impact of Wellness my Way on chronic disease risk factors of consumers?	Effectiveness
4. How many local organizations partnered with Wellness my Way for implementation in South West Queensland?	Adoption
5. What was the fidelity of the intervention delivery?	Implementation
6. How satisfied were consumers with Wellness my Way and their experience as a participant?	Implementation
7. What are the participants’ perceptions of their experience participating in Wellness my Way?	Implementation
8. What are the community stakeholders’ perceptions of their experience participating in Wellness my Way?	Implementation
9. What are the preventive health counselors perceptions of delivering Wellness my Way?	Implementation

a RE-AIM: Reach, Effectiveness, Adoption, Implementation, and Maintenance.

### Measures

#### Reach

Engagement with Wellness my Way was described as the number of consumers who initiate and complete a health and well-being assessment, engage with telephone coaching to co-design a well-being action plan, and accept referrals to prevention programs. These outcomes were analyzed using data from Queensland Health’s HCC’s Microsoft Dynamics 365 customer relations management (CRM).

#### Effectiveness

##### Uptake of Prevention Programs

The impact of Wellness my Way on participation in prevention programs in South West Queensland was assessed by examining the number of referrals that consumers action. Overall engagement of South West Queensland consumers in prevention services (programs directly or indirectly embedded within Wellness my Way) will be analyzed. Prevention programs were asked to report total program engagement before and during the implementation of the Wellness my Way pilot.

##### Chronic Disease Risk Factors

The impact of Wellness my Way on consumers’ chronic disease–related risk factors and diagnosis was assessed at program intake via the health and well-being assessment and 6 months post engagement with Wellness my Way via a digital or phone survey. Data were collected by Queensland Health’s HCC’s Microsoft Dynamics 365 CRM. Both the health and well-being assessment and the 6-month survey measured diabetes risk using a modified version of the Australian Diabetes Risk Assessment Tool (AUDRISK) [24], mental health using an ultra-brief screening tool (4-item Patient Health Questionnaire [PHQ-4]) [25], physical activity engagement using The Active Australia Survey [26], and other modifiable risk factors such as drug and alcohol use and biometrics.

##### Adoption

Adoption was measured by reporting the number of local organizations that partner with Wellness my Way to support the community-led implementation of the program. This outcome was reported using data collected by Health and Wellbeing Queensland.

### Implementation

#### Fidelity

Intervention fidelity was evaluated by reporting the completion rate for the components of the model of care (health and well-being assessment, telephone coaching). These outcomes were analyzed using data from Queensland Health’s HCC’s Microsoft Dynamics 365 CRM.

#### Consumers

Consumers’ satisfaction and experience with the Wellness my Way pilot were collected via the Patient Reported Experience Measures survey following the health and well-being assessment or telephone coaching call. The survey was sent to consumers who completed the model of care and those who drop out after the health and well-being assessment. Consumers were asked to provide feedback on the prevention model of care via level of agreement using Likert scale items and open text responses.

#### Stakeholders

Stakeholders’ perceptions and experiences of participating in the Wellness my Way pilot were evaluated via a qualitative in-person workshop, semistructured interviews, and focus groups. Program stakeholders including Connectors and HCC preventive health counselors were invited to offer their experience during the pilot implementation.

### Statistical Analysis

All quantitative reach, effectiveness, adoption, and implementation outcomes will be described using descriptive statistics. *χ*^2^ tests of association will be used to examine associations between categorical variables, and paired independent *t* tests and McNemar tests will be used to examine changes in continuous and categorical outcomes, respectively, between program intake and at 6 months. To be eligible to be included in the quantitative evaluation, participants must have been eligible for their 6-month follow-up at the close of the pilot implementation phase. Intention-to-treat analysis will be followed to handle missing data. The effectiveness outcome will be treated as exploratory given the pilot study design and absence of randomization or a comparison group.

All qualitative implementation data will be analyzed according to Braun and Clarke’s [32] approach to thematic analysis. Audio-recorded qualitative data will be transcribed verbatim, checked for accuracy, and deidentified for anonymity. Using NVivo 14 (version 14.3.2; Lumivero), researchers will generate initial codes and meet to group codes into relevant themes. Themes will be refined, and subthemes may be generated to assist interpretation of findings. Open-ended responses will be analyzed using content analysis [33].

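### One inclusion rule tied to 6-month follow-up covers the whole quantitative evaluation, including the primary reach count, and its cut-off is not dated

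*Protocol article*

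**What the plan says.** The Statistical Analysis section opens with a statement of coverage: "All quantitative reach, effectiveness, adoption, and implementation outcomes will be described using descriptive statistics". After naming the tests, including those for change between intake and 6 months, it sets the condition for entry. "To be eligible to be included in the quantitative evaluation", it says, "participants must have been eligible for their 6-month follow-up at the close of the pilot implementation phase". No outcome is exempted.

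The opening of Methods gives the calendar. The pilot was "delivered from July 29, 2024, to June 30, 2025, with follow-up data collection until January 29, 2026". Delivery and follow-up are therefore two periods with different end dates. The Abstract, under Results, says: "The Wellness my Way pilot program within South West Queensland, Australia, concluded in January 2026". The main Results section attaches the date 29 January 2026 to the end of the pilot evaluation.

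The Abstract and the Objectives section make uptake (reach) primary. Under Measures, Reach, the definition begins: "Engagement with Wellness my Way was described as the number of consumers who initiate and complete a health and well-being assessment". It goes on to coaching and accepted referrals. Fidelity is the completion rate of the assessment and the coaching. Satisfaction comes from a survey sent after the assessment or the coaching call.

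**The concern.** A rule about being due for a 6-month survey makes sense for a pre-post comparison. It has no role in counting who started an assessment, took a coaching call or accepted a referral. Applied as worded, it can shrink the primary outcome for a reason unrelated to reach. It can do the same to the consumer-level fidelity and satisfaction results.

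The cut-off is also loose. The article does not say when the implementation phase closed, and the dates it gives allow two candidates seven months apart. The population behind the primary outcome depends on which is used, and an analyst could settle that after seeing the data.

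**Working it through.** The article states no figure for the share of consumers that the rule keeps, so there is nothing to reproduce. The check is calendar arithmetic.

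**Inputs**
- Delivery: 29 July 2024 to 30 June 2025 (Methods, opening).
- End of follow-up data collection: 29 January 2026 (Methods, opening).
- Follow-up survey: 6 months after engagement (Measures, Chronic Disease Risk Factors).
- First counselor contact: within 1 week of the assessment (Model of Care). Used only as a sensitivity check, with a 7-day lag.
- Assumption: intake could occur on any day of the delivery period.

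**Step 1. Length of the delivery window.** 29 July 2024 to 30 June 2025, inclusive, is 337 days.

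**Step 2. Close taken as 30 June 2025.** A consumer qualifies if the engagement date plus 6 months falls on or before 30 June 2025. Share removed = (337 − days kept) / 337.

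| Definition of 6 months | Last qualifying day | Days kept | Days removed | Share removed |
|---|---|---|---|---|
| 180 days | 1 Jan 2025 | 157 | 180 | 53.4% |
| 6 calendar months | 31 Dec 2024 | 156 | 181 | 53.7% |
| 182 days | 30 Dec 2024 | 155 | 182 | 54.0% |
| 183 days | 29 Dec 2024 | 154 | 183 | 54.3% |

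If the 6 months run from a coaching call 7 days after the assessment, the share removed is 55.5% to 56.4%. More than half of the window goes under every definition tried.

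**Step 3. Close taken as 29 January 2026.** All 337 days qualify under every definition, with or without the lag. Share removed = 0 / 337 = 0%.

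**Step 4. Whether follow-up was long enough for everyone.** 30 June 2025 plus 6 calendar months is 30 December 2025. From then to 29 January 2026 is 30 days. Follow-up continued for 213 days after delivery ended, so each consumer could fall due before data collection stopped. On the Step 2 reading, everyone retained was already due by 30 June 2025, and those 213 days would serve mainly people whom the rule leaves out.

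**Step 5. Which outcomes need the rule.**

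| Outcome | Unit | Needs 6-month contact? |
|---|---|---|
| Reach (primary) | Consumer | No |
| Fidelity | Consumer | No |
| Satisfaction and experience survey | Consumer | No |
| Change in risk factors | Consumer | Yes |
| Adoption | Organization | Not touched by a rule about participants |

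**The case against.** The strongest reply is that this is one loosely scoped sentence in a condensed article. It directly follows the description of the intake-to-6-month tests and precedes the sentences on missing data and the exploratory effectiveness outcome. The Reach section carries no 6-month condition. The authors may well have meant the pre-post analyses only. That is plausible, but the sentence says otherwise, and the paragraph in which it stands has just listed reach as a quantitative outcome.

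A second reply is that the 54% holds on one reading only. The Methods opening gives 30 June 2025 as the end of delivery and does not call that period the implementation phase. The Abstract can be read as placing the end in January 2026, and then no one is lost by date. Being eligible could also mean qualifying for a follow-up still to come, which again loses no one. This stands: the 54% is conditional. The three date statements also fit together if the pilot is taken to include follow-up, so the fault is in terminology more than in outright contradiction.

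Four stronger readings may tempt a reader, and the article does not support them.
- **That consumers who joined from January to June 2025 are definitely dropped.** This depends on the undated close.
- **That season is fully confounded with the program.** Under the 30 June 2025 reading, intakes run from late July to December, which spans winter to summer. With uniform intake and a sinusoidal yearly cycle peaking in mid-January, the mean 6-month seasonal change is about 0.02 of the amplitude, against roughly 0.16 to 0.17 in size over the full window. A spring-autumn contrast would remain (about 1.46 of the amplitude, against about 0.01 or less over the full window). That is a narrower matter, in an analysis already labeled exploratory.
- **That adoption is affected.** It counts organizations, and the rule concerns participants.
- **That people who only began or completed an assessment can never become due for follow-up.** The article does not say who is sent the 6-month survey.

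**Conclusion.** The point holds in two parts. First, the scope is wrong as written: a 6-month condition is placed on the primary reach count and on fidelity and satisfaction, none of which uses 6-month data. This does not depend on the date. Second, the cut-off is undefined, and the consequence runs from 0% to about 54% of the delivery window (53.4% to 56.4% across definitions and lag). The upper figure follows from the more natural reading, in which the implementation phase is the delivery period and is distinct from follow-up. On that reading the pre-post sample is cut as well, without need, because follow-up was long enough for everyone.

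The percentage is a share of calendar time. It equals a share of consumers only if intake was uniform over the 337 days. Monthly enrolment is not given, so the true share could be higher or lower.

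**What to change.** 1. Confine the inclusion rule to the intake-to-6-month analyses, and state it as being due for 6-month follow-up by 29 January 2026.
2. Report reach, fidelity and satisfaction on all consumers who initiated an assessment from 29 July 2024 to 30 June 2025.
3. Use one term and one date for the end of delivery, and another term and date for the end of follow-up. Apply them consistently in the Abstract (Results), the opening of Methods, Statistical Analysis and the main Results section.

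The cost is wording only. The article states that data collection has ended, and the dates above allow every consumer engaged during delivery to fall due within it. The change should be made, and dated, before the analysis is run, so that the population for the primary outcome is not chosen with the results in view.
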